### Secondary outcomes

#### Complications/Cuff integrity

A standardized complications checklist has been developed. This will be used to monitor infection rate and other known post-surgical problems. MRI will be used to detect repair failure at 1 year post-operatively. Examination of the rotator cuff using MRI is highly correlated to surgical findings for full thickness tears, having a sensitivity and specificity of 85% and 83% for first-time shoulder surgery, and 84% and 91% for failed repairs [45]. For the purposes of this study, all MRI series will be reviewed by radiologists with special expertise in musculoskeletal imaging. The radiologists will conduct all measurements from the MRI images and will remain blinded to group allocation. Patients for whom MRI is contraindicated will be examined by ultrasound. Patients will undergo an MRI of the rotator cuff at 12 months post-operatively to evaluate cuff integrity. This is an appropriate time to ascertain whether the repair remains intact, as further biological recovery is unlikely. Cuff failure at this point may require revision surgery. Furthermore, delay of MRI would risk losing this key information if patients are lost to follow-up between the 1 and 2-year time points. Specifically, the MRI will document the size of the defect in the proximal to distal, humeral to bursal, superior to inferior direction in all four tendons, the muscle atrophy using the tangent sign (supraspinatus only), and the degree of fatty infiltration (supraspinatus and infraspinatus) as defined in previous work [7]. The appearance of the biceps tendon and any tear will be described (normal, tendinosis, partial-thickness tear (thinned or longitudinal split), or complete tear) and measured. Changes in the size of tear, muscle atrophy, and degree of fatty infiltration from the pre-operative state will be determined. This procedure has been used in an ongoing trial based at McMaster University and data collection will follow the same standardized format.

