In our primary analysis we will use an analysis of covariance (ANCOVA), where the baseline WORC score is used as a covariate, to compare the quality of life (WORC score) at 2 years post-operatively[88-91]. As a secondary analysis, we will conduct the same statistical test but will include age and tear size as covariates with the baseline score. All outcome measures with a continuous metric will be analyzed in the same manner (ASES, range of motion, MRI (degree of muscle atrophy, degree of fatty infiltration, remaining tear size), Work Limitations, strength, and SF-12). We will also conduct a repeated-measures ANCOVA to determine whether quality of life (as the primary outcome) changed differently over time between groups.

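### The MRI outcomes are assigned to a continuous-outcome ANCOVA, which fits a sign, a probable grade and a zero-heavy tear size poorly and cannot by itself answer the cuff-integrity objective

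*Protocol article*

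**What the plan says.** Planned analyses sets the primary analysis as an ANCOVA with baseline WORC as covariate, "to compare the quality of life (WORC score) at 2 years post-operatively". It then extends the method: "All outcome measures with a continuous metric will be analyzed in the same manner". The list that follows includes "MRI (degree of muscle atrophy, degree of fatty infiltration, remaining tear size".

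Complications/Cuff integrity describes what the radiologists will record. For the muscle it is "the muscle atrophy using the tangent sign (supraspinatus only), and the degree of fatty infiltration (supraspinatus and infraspinatus) as defined in previous work". For the tendon, "the MRI will document the size of the defect in the proximal to distal, humeral to bursal, superior to inferior direction in all four tendons". Changes from the pre-operative state are also to be derived. The purpose of the scan is stated: "MRI will be used to detect repair failure at 1 year post-operatively". That section sets the post-operative scan at 12 months and explains why a later scan was not chosen. Planned analyses gives no time point for the MRI outcomes.

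Secondary objectives names cuff integrity as one of the outcomes to be compared and describes restoring integrity and function as the direct intent of the repair.

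**The concern.** The method named in one section does not match the measures described in the other.

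- **Muscle atrophy.** Planned analyses treats it as a degree on a continuous metric, but the reading named is a sign. The word suggests a present/absent reading, and the article describes no other scoring.
- **Fatty infiltration.** It is also a degree, on a scale the article does not reproduce. An ordered grade is the likely form.
- **Remaining tear size.** This is a true length, but every intact repair contributes exactly zero. Its mean is the failure rate multiplied by the average size of a failure.

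The third item matters most. The scan is meant to show whether the repair held. The only integrity quantity that the article assigns to a named analysis is a mean in which a change in failure rate and a change in defect size can offset each other. Two arms could differ clearly in how often repairs fail and show no difference in the planned comparison.

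**Working it through.** **The plan's own figures.** The article gives no effect size, failure rate or power for any MRI outcome, so there is no MRI figure to reproduce. Its WORC calculation does reproduce: 2 × (1.96 + 0.84)² × 450² × (1 − 0.55²) / 142.5² = 109.07, stated as 109 per group. Then 109 × 1.15 = 125.35, about 250 in total. This serves only to fix the number of patients for what follows: 125 × 0.85 = 106 per arm with follow-up.

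**Step 1: what the mean measures.** Take intact to mean no measurable defect. Then

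mean remaining size = P(failure) × mean size among failures.

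With assumed rates:

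- Arm A: 0.10 × 2.0 cm = 0.20 cm
- Arm B: 0.20 × 1.0 cm = 0.20 cm

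The failure rate doubles and the difference in means is zero. These rates were chosen to cancel; they show what can happen, not what is expected.

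**Step 2: simulation.** Inputs, all assumed except the eligibility ceiling of 3 cm (Inclusion/Exclusion criteria), alpha of 0.05 and the 106 per arm above:

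- baseline size uniform from 0.3 to 3 cm;
- residual size zero if intact, otherwise a random fraction of baseline averaging 0.5;
- 4,000 runs per scenario.

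ANCOVA on residual size with baseline size as covariate was compared with a two-proportion test of defect present or absent.

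| Failure rates | ANCOVA on size rejects | Intact/failed test rejects |
|---|---|---|
| 10% vs 10% | 4.5% | 5.0% |
| 20% vs 20% | 5.0% | 6.0% |
| 30% vs 30% | 4.9% | 4.7% |
| 10% vs 25% | 66.4% | 83.2% |
| 20% vs 38% | 64.4% | 83.5% |
| 30% vs 50% | 64.6% | 84.4% |

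The first three rows show that ANCOVA roughly holds its type I error at this size despite the zeros. The last three show a loss of about 17 to 20 points of power compared with the binary outcome.

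**Step 3: offsetting effects.** One arm fails in 20% with residual size averaging 0.75 of baseline; the other fails in 37.5% with residual size averaging 0.40. The products are 0.20 × 0.75 = 0.15 and 0.375 × 0.40 = 0.15. With mean baseline (0.3 + 3)/2 = 1.65 cm, both means are 0.15 × 1.65 = 0.25 cm. ANCOVA rejected in 4.6% of runs, which is its null rate, and the intact/failed test in 80%.

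**Step 4: the other two readings.** No arithmetic applies. A continuous metric in Planned analyses stands against a sign, and a degree on a scale defined elsewhere, in Complications/Cuff integrity. If the sign is scored present or absent, a mean-difference model does not suit how it is recorded. If fatty infiltration is graded, the same model treats the steps between grades as equal.

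**The case against.** The strongest reply is that the sentence in Planned analyses covers continuous outcomes only. Repair failure is not one of them, so its analysis may sit in a fuller document not shown here. That is fair, and a reader should not infer that failure will go unanalysed. The point does not rest on that silence. It rests on what the article does fix: three MRI readings classed as continuous, against its own account of how they are read.

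Four stronger readings are tempting and are not supported.

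- *A 2-year MRI analysis is planned that cannot be run.* The 2-year time point is attached to the WORC, and the shared manner can mean the ANCOVA method alone. Complications/Cuff integrity clearly sets MRI at 12 months. What stands is that Planned analyses should name that time point, particularly as the abstract lists outcomes up to 24 months and mentions radiologists among the assessors.
- *ANCOVA intervals for tear size are unreliable.* Null rejection was 4.5–5.0% in the simulation, which does not support this.
- *Fatty infiltration is certainly ordinal and the tangent sign certainly binary.* Neither scoring is given in the article. Both are inferences from the words used.
- *Ultrasound patients will lack comparable measures.* Ultrasound is reserved for patients in whom MRI is contraindicated, and the article does not say what it will record.

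It is also true that tear size is a genuine measurement with planned pre-operative values, so ANCOVA is feasible, and that limiting size to failed repairs would replace a randomised comparison with a subset formed after randomisation. Both objections stand and shape the remedy.

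**Conclusion.** The point holds in a limited form. The article classes as continuous a reading that it describes as a sign and another that is probably a grade, and it sends to ANCOVA a tear size whose mean cannot separate the frequency of failure from its extent. For tear size the cost is interpretation and power: about 17 to 20 points in the scenarios tried, and a difference in failure rate missed altogether when the two components offset. Those figures depend on assumed failure rates and defect sizes, and on intact meaning zero defect; the article supplies none of them. Type I error is not the problem. The primary WORC analysis is untouched, and only secondary outcomes are affected. The change is still worth making, because cuff integrity is a stated objective and the same scans can answer it better.

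**What to change.** In Planned analyses:

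1. State that the MRI outcomes are those at 12 months.
2. Make intact versus failed repair the main integrity comparison, analysed as a binary outcome by logistic regression adjusted for pre-operative tear size, with the risk difference reported.
3. Take the tangent sign out of the continuous list, state how it is scored, and analyse it as binary.
4. State the fatty-infiltration scale. If it is graded, use an ordinal model adjusted for the pre-operative grade.
5. Keep remaining tear size as a supporting comparison of all randomised patients, by a rank or two-part method. Report size among failed repairs as description only.

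The cost is a few lines of text and a little more analysis work. The scans and readings do not change, and the wording can be settled before outcome data are seen.

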**Methods/Design:**

This randomized, multi-centre, national trial will determine whether an arthroscopic or mini-open repair provides better quality of life for patients with small or moderate-sized rotator cuff tears. A national consensus meeting of investigators in the Joint Orthopaedic Initiative for National Trials of the Shoulder (JOINTS Canada) identified this question as the top priority for shoulder surgeons across Canada. The primary outcome measure is a valid quality-of-life scale (Western Ontario Rotator Cuff (WORC)) that addresses 5 domains of health affected by rotator cuff disease. Secondary outcomes will assess rotator cuff functionality (ROM, strength, Constant score), secondary dimensions of health (general health status (SF-12) and work limitations), and repair integrity (MRI). Outcomes are measured at baseline, at 6 weeks, 3, 6, 12, and 24 months post-operatively by blinded research assistants and musculoskeletal radiologists. Patients (n = 250) with small or medium-sized cuff tears identified by clinical examination and MRI who meet eligibility criteria will be recruited. This sample size will provide 80% power to statistically detect  a clinically important difference of 20% in WORC scores between procedures after controlling for baseline WORC score (α = 0.05). A central methods centre will manage randomization, data management, and monitoring under supervision of experienced epidemiologists. Surgeons will participate in either conventional or expertise-based designs according to defined criteria to avoid biases from differential surgeon expertise. Mini-open or all-arthroscopic repair procedures will be performed according to a standardized protocol. Central Adjudication (of cases), Trial Oversight and Safety Committees will monitor trial conduct. We will use an analysis of covariance (ANCOVA), where the baseline WORC score is used as a covariate, to compare the quality of life (WORC score) at 2 years post-operatively. As a secondary analysis, we will conduct the same statistical test but will include age and tear size as covariates with the baseline score. Enrollment will require 2 years and follow-up an additional 2 years. The trial will commence when funding is in place.

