### Sample size

We have previously completed a non-randomized pilot study (n = 36, [name]) comparing mini-open to all-arthroscopic rotator cuff repair and have data representative of the population we wish to sample for this study. We piloted a number of study outcomes, but our calculations are based on our planned primary outcome measure (WORC). From our pilot data, the baseline WORC scores were 1345/2100 (SD = 324) for mini-open patients and 1463(287) for arthroscopic repair. At 1 year, patients in the mini-open group had a mean score of 712.5 (SD = 650.7) and the patients in the all-arthroscopic group had a mean score of 940.6 (a difference of 228 points on the WORC). In our estimates of sample size requirements, we have used an estimated standard deviation of 450 since we suspect that the standard deviation observed in the pilot study at 1 year is larger than that expected at 2 years since patients are expected to be more stable in their outcomes by this time point. Further evidence to support our hypothesis comes directly from our pilot data where the estimate of standard deviations from the baseline assessment was 287 and 325. We will perform an analysis of covariance (ANCOVA) using the baseline WORC scores as a covariate to determine whether there is a statistically significant and clinically important difference between treatment groups at 2 years post-operative. We defined a clinically important difference as a 20% difference in the mean score between groups [47]. We used the following equation to calculate the sample size:

Calculation: N per group = 2((Z_α _+ Z_β_)^2^σ^2^(1-r^2^))/(δ)^2^, Where:

α = the probability of making a Type I error = 0.05

1-β = the power to detect a difference if one truly exists = 0.80, thus, β = 0.20

δ = 20% of the baseline mean score = 142.5*

r = correlation between baseline and post-operative data = 0.55

σ = standard deviation = 450

N per group = 2((1.96 + 0.84)^2 ^(450)^2^(1-0.55^2^))/(142.5)^2 ^= 109 patients per group

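### The repeated-measures ANCOVA for the WORC recovery course is, in its classical form, complete-case and covariance-restricted; a mixed model on all available scores would do better at almost no cost

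*Protocol article*

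**What the plan says.** Planned analyses sets out two kinds of WORC analysis. The main one uses a single time point, 2 years: "In our primary analysis we will use an analysis of covariance (ANCOVA), where the baseline WORC score is used as a covariate". A second version adds age and tear size. The analysis at issue here is the additional one: "We will also conduct a repeated-measures ANCOVA to determine whether quality of life (as the primary outcome) changed differently over time between groups". It is the only planned test that uses the WORC course rather than the 2-year value.

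The Abstract (Methods/Design) gives the schedule: outcomes are taken "at baseline, at 6 weeks, 3, 6, 12, and 24 months post-operatively", so there are five post-operative scores per patient.

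Sample size gives the figures on spread. At baseline in the pilot, "the baseline WORC scores were 1345/2100 (SD = 324) for mini-open patients and 1463(287) for arthroscopic repair". At 1 year the mini-open arm had an SD of 650.7; no 1-year SD is given for the other arm. For 2 years the calculation uses "σ = standard deviation = 450", because "we suspect that the standard deviation observed in the pilot study at 1 year is larger than that expected at 2 years". The only correlation given is 0.55, between baseline and post-operative scores.

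On missing data, Sample size inflates by 15% for withdrawal, loss to follow-up and crossover together. Control of biases relating to follow-up plans rescheduling of missed appointments and, for persistent non-attenders, self-report measures by telephone or internet.

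**The concern.** The classical repeated-measures ANCOVA needs a complete vector of outcomes. A patient with four of five WORC scores contributes nothing, and those who remain are selected by attendance. Its univariate group-by-time F test also needs sphericity. With scores running from 6 weeks to 24 months after surgery, and a spread that the authors themselves expect to change between 1 and 2 years, that is a doubtful assumption.

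At stake is the trial's only test of whether recovery differs in its course. Planned analyses says that both short-term and long-term outcomes are of interest, and the Background notes that faster recovery might be expected after arthroscopic repair. An analysis that discards partly observed patients, and may reject a little too often, serves that question less well than a readily available alternative.

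**Working it through.** **The plan's own figure.** None is stated for the repeated-measures analysis. The sample size for the 2-year ANCOVA reproduces: 2 × (1.96 + 0.84)² × 450² × (1 − 0.55²) / 142.5² = 2,214,702 / 20,306.25 = 109.07, so 109 per group; 109 × 1.15 = 125.4, so about 250 in total. This point does not touch it.

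**Loss of patients.** If a proportion m of scores is missing independently at each of five visits, the complete share is (1 − m)^5. The rates are assumed.

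| m | share complete | of 250 |
|---|---|---|
| 3% | 0.97^5 = 0.859 | 215 |
| 5% | 0.95^5 = 0.774 | 193 |
| 8% | 0.92^5 = 0.659 | 165 |

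Alternatively, treat the 15% allowance as loss of the 2-year score and let a proportion q of scores also be missing at each of the four earlier visits. Complete patients are then 250 × 0.85 × (1 − q)^4: about 212 for q = 0, and 188, 173 or 139 for q = 3%, 5% or 10%. This is pessimistic, because the 15% includes crossovers, whose scores may be complete. A likelihood-based model on all available scores keeps every patient with at least one post-operative WORC, up to 250.

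**Constant variance.** The ratio of 1-year to 2-year variance is 650.7² / 450² = 2.09. If r = 0.55 held at both visits, baseline adjustment would multiply both variances by 1 − 0.55² = 0.6975 and leave the ratio unchanged. Equal variance over time (compound symmetry) is therefore at odds with the stated figures.

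**Sphericity.** This needs the same variance c for every between-visit difference, so cov(i, j) = (s_i² + s_j² − c) / 2. The SDs alone cannot rule it out. Take SDs of 350, 400, 500, 651 and 450 (the first three assumed) and c = 200,000. A valid covariance matrix results, with correlations from 0.29 to 0.76. The pattern is odd, though: 6 weeks with 3 months gives (122,500 + 160,000 − 200,000) / 2 / (350 × 400) = 0.29, while 6 weeks with 12 months gives (122,500 + 423,801 − 200,000) / 2 / (350 × 651) = 0.76.

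More generally, let the 6-week and 3-month SDs both equal s, with S = 650.7 at 12 months. Equating the variances of the 6-week-minus-3-month and 6-week-minus-12-month differences gives

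r(6 wk, 3 mo) = 1 − (s² + S² − 2·r(6 wk, 12 mo)·s·S) / (2s²).

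With r(6 wk, 12 mo) = 0.55, this is 0.25 for s = 450 and −0.21 for s = 350. Whenever S exceeds s, the adjacent visits must correlate less than the distant ones. That is implausible but not impossible.

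**Type I error.** Simulated null trials used the univariate group-by-time F test on complete data. Epsilon is (tr A)² / (4·tr A²), where A is the doubly centred covariance matrix of the five scores.

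- SDs 350, 400, 500, 651, 450; 109 per arm; 6,000 trials; AR(1) correlation 0.6 to 0.9: about 6.5% to 8.2% uncorrected, epsilon 0.73 to 0.56.
- Three other SD paths ending in 650 then 450; 106 per arm; 4,000 trials; AR(1) 0.7: 6.0% to 7.4%, epsilon 0.68 to 0.73.
- The same three paths with exchangeable correlation 0.55: 5.3% to 6.2%, epsilon 0.83 to 0.98.
- Equal SDs with AR(1) 0.7: 6.4%, epsilon 0.69.
- With a Greenhouse-Geisser adjustment in the 4,000-trial runs (true epsilon used): 4.3% to 5.4%.

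The equal-SD run shows that the assumed correlation pattern drives much of the excess; it does not come from the stated SDs alone.

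**The case against.** The strongest reply is that one sentence in a journal article names a family of methods. It does not prescribe listwise deletion, an uncorrected F test or a covariance structure. The same label is sometimes used for likelihood-based models, and such details commonly sit in a full protocol or SAP that is not shown. This stands to the extent that the faults above belong to the classical form and cannot be reported as what the trial will do. It does not remove the point, because the named method in its ordinary sense is the weaker choice and nothing in Planned analyses points to a mixed model.

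A reader might also infer that the stated SDs prove that sphericity fails. They do not: between-visit correlations are not given, a spherical matrix with such SDs exists, 650.7 comes from one arm of a 36-patient non-randomised pilot, and 450 is an assumption. Unequal spacing of visits does not break sphericity by itself either.

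The missing-visit rates are assumed, and independence overstates the loss if the same patients miss several visits. WORC is self-reported, so telephone or internet collection can recover scores after a missed clinic visit. All this stands and lowers the likely size.

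Finally, an omnibus group-by-time test does answer the question as worded. The article states no hypothesis for a particular early visit, so contrasts at 6 weeks or 3 months would be an addition, and their absence is not an error.

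**Conclusion.** The point holds as an improvement to a supplementary analysis. In its classical form the named method discards partly observed patients and leans on a covariance assumption that the stated SDs make unlikely but do not refute.

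The loss of patients matters more: 14%, 23% or 34% would be excluded at 3%, 5% or 8% independent missingness per visit, and fewer if gaps cluster or are recovered. An epsilon correction, or the multivariate version of the classical test, would deal with sphericity but would still need complete vectors.

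The type I error excess is modest: about 6% to 8% when correlation falls with distance between visits, about 5% to 6% when it is exchangeable, and close to 5% after correction. These figures rest on assumed correlations and assumed early SDs.

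It would be wrong to conclude that the main result is at risk: the 2-year ANCOVA and the sample size of 250 do not depend on this analysis.

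**What to change.** Replace the sentence on repeated-measures ANCOVA with one along these lines: the course of WORC will be compared between arms with a mixed model for repeated measures, fitted by restricted maximum likelihood to all available post-operative WORC scores, with arm, visit, arm-by-visit, baseline WORC and baseline-by-visit as fixed effects and an unstructured within-patient covariance; the arm-by-visit test addresses whether the course differs. Optionally, report the arm difference with its confidence interval at each visit, to show when any difference arises.

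The cost is one sentence, standard software and no added data. An unstructured matrix for five visits has 15 parameters (5 × 6 / 2), which about 218 to 250 patients can support. The model assumes that scores are missing at random given the observed ones; this is weaker than what an unbiased complete-case analysis generally needs, and should be stated. If a fuller protocol or SAP already specifies such a model, only the name in the article needs aligning.
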